#### Iconic therapy group

Iconic Therapy is a 12-week programme structured in 4 explicit manual-driven modules. Each module takes from 2 to 3 weekly group sessions with a duration of 90 min each: the first 30 min are to debate the practical use of last session’s icons and the next 60 to advance new ones. The programme content is focused on the essential impairments in personality functioning of BPD patients: intimacy/empathy, identity and self-direction as parts of a more general introductive module. A therapist and co-therapist will lead the group. Programme contents are summarised in Table 2.

**Table 2 Tab2:** Summary of the contents of Iconic Therapy and Structured Support Therapy programmes

Therapy group	Programme composition^a^
Iconic therapy + treatment as usual^b^	Module 1: Understanding the problem, motivating and acquiring some basic coping skills. Session 1 *Content:* *-* Presentation. - Explicative model of pathology: visual understanding of the problem origins and perpetuation as an enduring vicious cycle (*the sinking, the blinding and the flight icons*) - Education to recognize patient’s affective reactions (*the map icon*). *Objectives:* Understanding that it is possible to develop healthier alternatives to replace dysfunctional patterns of thinking, feeling and behaving (to be learnt and trained during the length of the therapy). Session 2 *Content:* - Therapeutic model elaboration: emotional self-regulation techniques (*the key phrase and the cooling off time icons*). - Basic skills training: decision making and self-improvement techniques to manage remorse after hurting another (*the corsage of alternatives, the telephone and the zig-zag icons*). *Objectives:* Acquiring new learning experiences and general self-management skills to control inappropriate emotional responses. Module 2: Intimacy and empathy. Session 3 *Content:* - Interpersonal problems solution: expressing criticism to reach an agreement (*the sacks attack and the translator icons*). - Practical examples and role-playing in groups. *Objectives:* Experiencing self-effectiveness when sharing experiences in interpersonal relationships. Session 4 *Content:* - Interpersonal problems: accepting criticism and getting distance from negative relationships (*the black grain, the glass wall and the rock wall icons*). - Practical examples and role-playing. *Objectives:* Sharing experiences of interpersonal relationships in groups. Session 5 *Content:* Negative emotions and cognition management: - Hostility (*the mountain icon*) - Inhibition (*the pen icon*) - High expectations from others (*the bouquet of flowers icon*) - Cognitive filters (*the coloured sunglasses icon*) - External attribution (*the tower of books icon*) - Practical examples and exercises. *Objectives:* Detecting and changing negative ways of perceiving and interpreting other people or events. Practicing motivated behaviors, reflecting intentions and desires. Module 3: Self-esteem and identity. Session 6 *Content*: - Personality trait optimization (*the river icon*). - Others comparison avoidance (*the coloured bars icon*). - Overcoming the need to receive a torrent of affection (*the self-disqualification pitfall icon*). - Mimetization vs reaching a genuine position (*the mimetization and the positioning icons*). *Objectives:* Gaining a more stable sense of self and personal security. Session 7 *Content*: - Sense of Emptiness (*the Matryoshka dolls icon*). - Negative vs positive behavioral tendencies (*the positives and negatives icon*). - Prejudices avoidance (*the Mozart icon*). *Objectives:* Gaining a more stable sense of self and personal security. Session 8 *Content*: - Emotional balance clues (*the table icon*). - Personal dependence avoidance (*the flag icon*). - Uselessness of complaining about past experiences and how to take advantages of them (*the web and the embankment phrase icons*). - Practical review by sharing practical uses of the icons on group. *Objectives:* Reaching independent self-advise on daily situations. Module 4: Self-direction. Session 9 *Content:* - Liberty vs impulse slavery: reconceptualization (*the bypass road icon*). - Goals setting (*the range icon*). *Objectives:* Strengthening impulsiveness and risk-taking control. Session 10 *Content:* - Adversity as an impulse towards the goal (*the sailboat icon*). - Values and prosocial standards to guide our decisions (*the compass icon*). - Practical exercises of people finding their own concretes and vital goals. *Objectives:* Instigating normative ethical behaviour. Final review (Session 11): Relapse prevention. Workshop reviewing learned strategies and post-treatment evaluation. Sixth month review (Session 12): Relapse prevention. Workshop reviewing learnt strategies. Twelveth month review (Session 13): Relapse prevention. Workshop reviewing learnt strategies and 12-month follow-up evaluation.
Structured support therapy + treatment as usual^c^	Session 1: Social relationships. *Content:* - Presentation. - Video and debate. May friends *or* acquaintances turn into relatives for you? / What is the importance of having a friend to stand by? / Is it possible to find a friend on the internet?. *Objectives:* Participants interacting with other participants of similar characteristics in a casual and secure environment. Session 2: Risks on the internet. *Content:* Video and debate. What do you use social websites for? selfies, finding partners, photos, risks, problems. *Objectives:* Participants interacting with other participants of similar characteristics in a casual and secure environment. Session 3: Emotional instability and impulse control. *Content:* - Information about the role of emotion regulation and emotional instability (coordinate axis) in emotional disorders. - Impulsivity definition. The turtle technique (detect the emotion, stop, hide and breathe in the shell, go out and think of a solution). *Objectives:* Debating about the given topics and sharing strategies to deal with them. Session 4: Emotional regulation and jacobson relaxation technique. *Content:* - Role-playing: The therapist reads a short story and the participants play a role simulating different attitudes towards the story (distracted, aggressive or interested). The rest of the participants try to detect name, intensity and coping skills to deal with shown emotions. - Soft music and Jacobson relaxation technique. *Objectives:* Session 5: Social skills. *Content:* - Defining empathy and assertiveness. - Role-playing “the assertiveness umbrella”: the participant with the umbrella is required to express his complaints in front of the rest of the group. *Objectives:* Learn to detect internal and external social skills. Session 6: Social skills ii. *Content:* - Role-playing. The participants are invited to introduce themselves, ask the therapists questions, maintain a conversation with their closer partner or express, in his/her opinion, the best characteristic of the partner on the left. *Objectives:* Increasing assertive behavior in a secure environment. Session 7: Self-image and communicational styles. *Content:* - Defining identity and self-image by thinking of an admired person (famous, family or friends) and detecting similar traits within themselves. - Defining communicational styles: passive, aggressive, assertive. - Videos with examples of people with different communicational styles. *Objectives:* Learning to detect their own and other’s necessities. Session 8: Mindfulness. *Content:* - A specialized volunteer psychologist delivers a mindfulness session lying on the floor, with raisins to be consumed by the therapist and participants as a shared contemplative experience. *Objectives:* Enhancing stress tolerance and contemplation capacity. Session 9: Self-esteem. *Content:* - Defining self-esteem and main personal characteristics: each participant writes his or her 5 main characteristics on an anonymous paper and gives it to the therapist, who reads them all. When there is a negative characteristic, the therapist tries to explain its usefulness and the way to make it positive. *Objectives:* Improving self-awareness. Session 10: Self-esteem ii. *Content:* - Self-esteem: participants are incited to exercise their body, trust in their qualities and use them, don’t look for other’s approval, take perspective and accept their problem. - Self- realization: bearing in mind their best qualities, participants are invited to think of an activity they are motivated for as well as different ways to keep in touch with it. *Objectives:* Improving the self-esteem. Session 11: Relapse prevention. Reviewing the strategies learned across the program and contents and post treatment evaluation. Sixth month review (Session 12): Relapse prevention. Workshop reviewing learnt strategies. Twelveth month review (Session 13): Relapse prevention. Workshop reviewing learnt strategies and 12-month follow-up evaluation.

Notes. ^a^All patients are free to contact the principal investigator throughout the process to solve practical questions about the use of session contents. ^b^10–12 group sessions given by 2 specifically trained psychologists using the guideline draft. ^c^11 group sessions given by 2 psychologists using a non-manualized program

A total of 3 more group sessions (2 of them matched with the assessment) will be delivered by the therapist and co-therapist after treatment and at 6 and at 12 months follow-up as well as an undetermined number of face-to-face sessions with the principal investigator. The same is true for the Structured Support Therapy group. These sessions are aimed to assure participants’ needs are met and to minimise dropout rates in both groups. Nevertheless, the Iconic Therapy group will continue to see and reinforce visual images, whereas those in the control group will receive plain verbal explanations without illustrations.

As this is the first time the Iconic Therapy programme is being delivered by therapists other than its creator or principal investigator, group sessions will be supervised from behind a unidirectional window by the principal investigator. Also, two Iconic Therapy randomised group sessions will be recorded by the creator for analysis. During the 10–12 week period of the study, supervision and feedback will be given to the therapist and co-therapist of both study groups.

#### Structured support therapy group

Participants will take part in a 60-min weekly group session for 10–12 weeks. Sessions will be 30 min shorter than those for the Iconic Therapy group, as verbal explanations do not require further practical clarifications by therapists and a longer duration could affect the adherence. For the second part of the programme, 3 group sessions and a variable number of individual face-to-face sessions will be offered to this group, same as for the Iconic Therapy group. The aim of face-to-face sessions is to meet the needs of participants and to provide support throughout the study. The contents of the programme can be seen in Table 2.

#### Treatment as usual

Patients in the trial will continue their ambulatory treatment from public specialised mental health services as usual. TAU may include medication with weekly or monthly individual sessions with the referring psychologist.

#### Therapy attendance and compliance

At the 12-month follow-up, the trial for both groups will have concluded. A participant has to attend a minimum of 8 group sessions to be considered as having completed treatment.

#### Data collection and outcome measures

Table 1 displays the outcome measures and corresponding instruments and assessment times. Patients will be assessed at baseline, after treatment and at 12-month follow-up.

#### Primary outcome measure

##### Severity of borderline personality disorder

We will use the Spanish version of the BSL-23 [44]; it replicates the one factor structure of the original and shows high reliability (*α* = .95) as well as good test-retest stability when checked in a subsample of 74 patients (*r* = .73 *p* < .01). The BSL-23 [45] is one of the most widely used questionnaires (in its short form) in psychotherapy trials. It has 23 self-answer questions rated on a scale of 1 to 5 on the Likert scale, ranging from 0 (not at all) to 4 (very strong). The BSL-23 is very reliable in the diagnosis of BPD, and as evidenced by Cronbach’s alpha of .93, its one factor structure makes it highly constant.

#### Secondary outcome measure

##### Suicidal ideation and behaviour

The C-SSRS [40] is a validated tool for quantifying the existence or severity of suicidal ideation and behaviour. It has 2 sub-scales to assess ideation and behaviour separately. Ideation severity is assessed on a 5-point Likert scale within a range of 1–5. The existence of suicidal behaviour is assessed in the same manner. This ranges from 0 (very little/no physical harm) to 4 (intensive care service required). The C-SSRS demonstrates good convergent and divergent validity. Also, it displays high sensitivity and specificity for the classification of suicidal behaviour. We will provide a self-report form for the questionnaire.

##### Non-suicidal self-injury criteria

In this study, criteria from the DSM-V [1] regarding self-injury is used to assess participants.

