**Methods/Design:**

Our study will be a controlled 12-month pragmatic, two-armed RCT. A total of 72 young people (15 to 25 years old) with suicidal ideation/self-injuring behaviour and BPD traits and symptoms will participate in the study. The subjects will be randomised into two groups: Iconic Therapy or Structured Support Therapy. The participants will be assigned to either group on a 1:1 basis. Both the Iconic Therapy and the Structured Support Therapy programmes consist of 11 weekly sessions delivered by two trained psychologists in a group format of between 8 to 12 outpatients. The primary outcome will be measured by the change in symptom severity. Secondary outcomes include changes in suicidal ideation/ behaviour, non-suicidal self-injury, maladjustment to daily life and cost-effective analysis. The primary outcome will be a decrease in the severity of BPD symptoms as assessed by the Borderline Symptom List (BSL-23). For the clinical evaluation, three study assessments will take place: at baseline, after treatment and at 12-month follow-up. We hypothesise that patients attending the Iconic Therapy group will show a significantly higher reduction in symptoms than those in the Structured Support Therapy group. Data will be analysed using generalised estimating equation (GEE) models.

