## Methods

### Study design

The study is planned as a 12-month pragmatic, two-armed parallel randomised controlled trial (RCT). It will randomise 72 young subjects (aged between 15 and 25) with suicidal ideation and/or self-injuring behaviour and borderline personality traits. Participants will be randomly assigned to one of two groups, Iconic Therapy or Structured Support Therapy, on a 1:1 basis to form 4 groups of 18 patients. Two of these groups will be included in the Iconic Therapy group and the other two in the Structured Support Therapy group. A total of 8 volunteer psychologists will administer the therapies formed into 4 pairs of therapists and co-therapists. The volunteer psychologists are required to have obtained a Master’s Degree in Psychology and have previous experience with patients. It is inherently not possible to blind psychologists delivering the Iconic Therapy intervention, since they have been specifically trained for 10 months. The goal of the psychologists conducting the control group is to obtain good clinical results. They will achieve this through therapeutic intervention.

Primary and secondary outcome measures will be assessed at baseline, after treatment (10–12 weekly sessions) and at 12-month follow-up (15 months after the baseline). Study variables and assessment times are shown in Table 1.

**Table 1 Tab1:** Study variables and assessment time

Instrument	Assessment area	Time of assessment
Primary outcomes		
BSL-23^a^	BPD symptoms severity	Baseline After treatment At 12 months
Secondary outcomes		
C-SSRS^b^	Suicidal ideation or behaviour	Baseline After treatment At 12 months
DSM-V criteria^c^	Non-suicidal self-injury diagnosis	Baseline After treatment At 12 months
CSRI^d^	Economic evaluation	Baseline At 12 months
Subsidiary measures		
IG^e^	Daily life adjustment	Baseline After treatment At 12 months
CEQ^f^	Credibility/expectancy questionnaire	After treatment At 12 months
Ad hoc scales^g^	Perceived subjective global improvement *(self-reported)*	After treatment At 12 months
Ad hoc scales^h^	Perceived global improvement *(family/friends reported)*	After treatment At 12 months

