#### Data analyses

Patients will be included in intent-to-treat analyses. Participants’ demographic characteristics will be summarised using descriptive statistics, and the comparability of the treatment groups will be examined using *χ*^2^ tests for categorical variables and *t* tests for continuous variables.

Data analyses of the primary and secondary outcomes will be conducted using generalised estimating equation (GEE) models. Essentially, GEE models extend generalised linear models (GLMs) to allow analysis of repeated measurements or other correlated observations. The response can be scale, counts, binary or events-in-trials. In addition, GEE models can also deal with data that have missing values as long as the missing value is completely random. Parameter estimation can still yield robust results [51].

In these GEE models, treatment conditions (experimental vs. control) will be included as the between-subjects factor and time (baseline, after treatment and at 12 month follow-up) as the repeated measure. Main effects and interaction between treatment and time will be examined. When the interaction effect is statistically significant, simple main effects analyses will be conducted.

IBM SPSS (version 22.0 for Windows) will be used for the statistical data analyses. Statistical significance will be defined as *p* < .05. Bonferroni correction will be applied for post hoc multiple comparisons.

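### Change in non-suicidal self-injury is measured only as a DSM-V diagnosis, which cannot register a fall in frequency among continuing cases and may carry pre-treatment episodes into the after-treatment rating

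*Protocol article*

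**What the plan says.** The abstract (Methods/Design) lists self-injury among the outcomes to be compared as change: "Secondary outcomes include changes in suicidal ideation/ behaviour, non-suicidal self-injury, maladjustment to daily life and cost-effective analysis". Table 1, under Study design, describes the measure as "Non-suicidal self-injury diagnosis", by DSM-V criteria, at baseline, after treatment and at 12 months. The section on non-suicidal self-injury criteria is a single sentence, saying that "criteria from the DSM-V [1] regarding self-injury is used to assess participants".

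On timing, Study design has outcomes "assessed at baseline, after treatment (10–12 weekly sessions) and at 12-month follow-up", and places the last of these 15 months after baseline. Under Data analyses, primary and secondary outcomes go into GEE models with treatment and "time (baseline, after treatment and at 12 month follow-up) as the repeated measure". The same section notes that GEE can take count as well as binary responses.

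The other behavioural instrument is the C-SSRS: "It has 2 sub-scales to assess ideation and behaviour separately". It is described as covering suicidal ideation and suicidal behaviour. The article names no count or frequency of non-suicidal self-injury as an outcome, and states no reference period for the DSM-V rating.

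**The concern.** A diagnosis sorts patients into cases and non-cases over whatever period its criteria use. That suits describing a sample at entry but is a blunt way to measure change, for two separate reasons.

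First, it discards frequency. A patient who self-injures much less often but still meets the criteria is scored as unchanged. The Discussion itself says that the frequency and lethality of self-injury will vary between participants, so much of the information on change may lie in what the category drops.

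Second, the first repeat comes only 10–12 weeks after the start. If the criteria look back further than that, the after-treatment rating partly re-counts behaviour from before treatment, in both arms. This would pull the after-treatment contrast towards no difference, at the visit where Study aims expects the effect on symptoms to appear first.

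**Working it through.** The article states no rate, effect size or power for self-injury, so there is no figure of its own to reproduce. The check has three parts.

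**1. Loss of frequency (no assumption about the look-back).** Suppose the criteria need at least *k* episodes in their window. A patient who goes from *a* episodes to *b*, with *a* > *b* ≥ *k*, is a case at both visits. The scored change is 0, whatever the size of *a* − *b*. A patient below *k* at baseline cannot show improvement at all. Such patients may be enrolled, because Study design admits suicidal ideation and/or self-injury and the inclusion criteria list ideation without requiring self-injury.

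**2. Share of the look-back lying before treatment.** Inputs:
- *t*, weeks from start to the rating. After treatment, *t* = 10–12 (Study design), taking baseline as the start of treatment. At the last visit, 15 months × 52/12 = 65 weeks.
- *L*, the look-back in weeks. It is not in the documents, so it is varied as an assumption.

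Formula: share before treatment = max(0, *L* − *t*)/*L*.

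| Assumed look-back | After treatment, *t* = 12 | After treatment, *t* = 10 | 15 months, *t* = 65 |
|---|---|---|---|
| 1 month (*L* = 4) | 0% | 0% | 0% |
| 3 months (*L* = 13) | 1/13 = 8% | 3/13 = 23% | 0% |
| 6 months (*L* = 26) | 14/26 = 54% | 16/26 = 62% | 0% |
| 12 months (*L* = 52) | 40/52 = 77% | 42/52 = 81% | 0% |

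At 15 months a 52-week window opens at week 65 − 52 = 13, after the 10–12 weeks of sessions. That visit is therefore free of pre-treatment time. With a look-back that long, however, no assessment would isolate self-injury during the treatment period.

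**3. What carry-over would do to the contrast (illustration only).** Assume that all patients are cases at baseline, that 50% stop in one arm and 25% in the other, and that a fraction *c* of those who stopped are still classed as cases. The case rate in an arm is 1 − (proportion stopping) × (1 − *c*), so the difference is 25 × (1 − *c*) percentage points. Power is two-sided with 26 per arm, the article's required number per group.

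| *c* | Case rates | Difference (points) | Power |
|---|---|---|---|
| 0 | 50.0% vs 75.0% | 25.0 | 46% |
| 25% | 62.5% vs 81.3% | 18.8 | 32% |
| 50% | 75.0% vs 87.5% | 12.5 | 21% |
| 75% | 87.5% vs 93.8% | 6.3 | 12% |
| 100% | 100% vs 100% | 0 | not applicable |

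The stopping rates and *c* are invented to show direction and scale. None of them comes from the documents.

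**The case against.** The strongest objection is that the carry-over problem depends on a figure the documents do not contain. The assumed range runs from no problem at 1 month to a serious one at 12 months, and nothing in the article favours the long end. The reference period used at each visit is also the kind of detail a condensed article leaves to the full protocol or the case report form. Both arguments stand: carry-over has to be stated as a conditional risk, and the unstated reference period is not in itself an error.

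Three stronger readings are tempting, and the documents support none of them.
- A reader might infer that patients who stop self-injuring will be counted as cases. That requires a look-back longer than 10–12 weeks, and also enough pre-treatment episodes left in the window to satisfy the criteria.
- A reader might infer that the 10–12 week rating is the only repeat. Table 1 repeats it at 12-month follow-up, where look-backs of up to 12 months include no pre-treatment time.
- A reader might infer that a real effect will be missed. What follows is possible attenuation of unknown size at one of two post-baseline visits.

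It can also be said that criterion counts or episode numbers may be recorded alongside the diagnosis. The article does not say so; Table 1 names a diagnosis.

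The objection does not reach the choice of measure. The article states the instrument, and the instrument is a category. The loss of frequency follows from that without any assumption about the look-back, and the C-SSRS as described does not fill the gap.

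**Conclusion.** The point holds in two parts of unequal strength.

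The unconditional part is that a DSM-V diagnosis, as the sole measure of change in non-suicidal self-injury, cannot register reduced frequency among patients who still meet the criteria. This rests only on Table 1 and on the abstract's listing of change in self-injury as an outcome.

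The conditional part is that a reference period longer than 10–12 weeks would place pre-treatment time inside the after-treatment rating, from 8–23% of the window at 3 months up to 77–81% at 12 months. The after-treatment contrast may then be attenuated. With a look-back of 10 weeks or less this does not arise.

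The reach is limited. This is one secondary outcome; the BSL-23 primary outcome and the sample size based on it are unaffected. It is worth correcting because the correction is cheap and fits the planned analysis.

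**What to change.** Keep the DSM-V diagnosis to describe the sample at baseline. Add, as the change outcome, the number of days with self-injury in one fixed recent window, for example the past 4 weeks. The window should be no longer than the treatment period, so that it lies wholly after the start of treatment at both later assessments, and the question should be worded identically at all three. Analyse it as a count in the GEE already planned, with treatment, time and their interaction.

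If the diagnosis is also reported after baseline, state the reference period used at each visit. If the full protocol already fixes that period, one sentence quoting it settles the conditional part.

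The cost is one extra question at assessments already scheduled, plus a change of wording in Table 1 and in the outcome section. The downside is that a short window misses rare events, so patients who self-injure seldom may report zero at every visit.
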